## Abstract

**Background:**

Intermittent theta burst stimulation (iTBS) is a noninvasive stimulation technique to induce neuronal and synaptic plasticity. The induced cortical plasticity is imperative in the recovery of motor and sensory functions. Spinal cord injury (SCI) causes damage to neurons and results in sensorimotor dysfunction. The effect of iTBS on recovery of motor and sensory dysfunction in complete SCI (cSCI) is still elusive.

**Objective:**

This study aims to assess the effect of iTBS on corticospinal tract integrity, plasticity, and regaining of motor and sensory function in patients with cSCI. The rationale behind using an iTBS protocol is to modify and augment the communication between spared neurons of the corticospinal tract and strengthen the synaptic transmission, which will improve motor function in underlying muscles.

**Methods:**

A total of 40 patients with cSCI with American Spinal Injury Association (ASIA) grade A, aged 18-60 years, were randomly assigned to 5 groups. To evaluate the efficacy of iTBS versus traditional repetitive transcranial magnetic stimulation, patients were categorized into placebo, repetitive transcranial magnetic stimulation, and iTBS. In addition, to determine the optimal site for stimulation, groups were further subdivided into motor cortex, spinal cord, and combined. Each patient underwent 10 iTBS sessions twice daily for 5 consecutive days. Neurological outcomes and functional outcome parameters will be assessed. Electrophysiological evaluations included transcranial magnetic stimulation single-pulse and paired-pulse parameters. The effect of iTBS intervention on biomarkers will be quantified using the enzyme-linked immunosorbent assay, while neurotransmitters will be quantified by liquid chromatography and tandem mass spectrometry. Measurements will be done before and after the intervention, with follow-ups at 1, 2, and 3 months.

**Results:**

The outcome of the study will be defined by electrophysiological parameters elicited by single- and paired-pulse stimulation, ASIA score, pain, activities of daily life, quality of life, anxiety, depression, and biomarkers related to SCI. The results of this study will uncover the effectiveness of iTBS stimulation on (1) recovery of motor and sensory function in cSCI, (2) excitability of the corticospinal tract, (3) neurological recovery and modulation of pain, and (4) cortical reorganization after injury.

**Conclusions:**

iTBS in conjunction with an individualized rehabilitation program may serve as an integrated strategy to rejuvenate locomotor abilities and improve the overall quality of life for people with cSCI.

**Trial Registration:**

Clinical Trials Registry- India CTRI/2022/11/047038; https://ctri.nic.in/Clinicaltrials/main1.php?EncHid=13361.98443

**International Registered Report Identifier (IRRID):**

DERR1-10.2196/66531

## Introduction

### Background

Spinal cord injury (SCI) is a neurological condition that causes progressive neurodegeneration. The major symptoms of SCI are paralysis, paresthesia, pain, spasticity, bladder, bowel, and sexual dysfunction. It largely affects the young population (21-49 years); thus, the psychological impact on a healthy individual to adapt to a paraplegic or quadriplegic condition in their early life is devastating. SCI causes damage to neurons, nerves, and other surrounding cells that send and receive signals from different body parts to the brain via the spinal cord (SC) and vice versa [1]. SCI can be traumatic or nontraumatic. Traumatic SCI is a great challenge for therapeutic management considering its high morbidity. There is complete or incomplete loss of locomotor, sensory, and autonomic functions depending on the severity and level of the lesion [2]. The consequences of injury are not just a break in communication between neurons, but a cascade of events that sets up a vicious cycle and leads to widespread neuronal degeneration, cell death, and the formation of glial scars [3]. Cellular components such as proteins, phospholipids, neurotransmitters, and metabolites derived from SC neurons and glial cells diffuse from the injury site into the cerebrospinal fluid and blood [4]. These biomarkers could serve as good diagnostic markers to predict the severity of the injury. To regain functional connectivity, and attenuate gliosis and secondary injury, activity-dependent strategies have been proposed to be quite effective. The current treatment modalities for SCI include surgery, pain management, and rehabilitation. However, functional recovery by restoring connections of the corticospinal tract after a complete SCI is challenging.

High-frequency repetitive transcranial magnetic stimulation (rTMS) has decreased neuropathic pain and spasticity in incomplete SC–injured patients [5,6]. A newer form of patterned transcranial magnetic stimulation (TMS), intermittent theta burst stimulation (iTBS) is now being studied for the improvement of symptoms in incomplete SCI [7]. There is very limited literature available, showing the effect of either cortical iTBS or trans-spinal TMS in combination with a rehabilitation program to promote repair, regeneration, and recovery in patients with complete SCI (cSCI). This study aims to determine the functional outcomes of administering iTBS at the cortex as well as at SC along with intensive rehabilitation programs in patients with cSCI.

### Study Objectives

This study aims to evaluate the comparative efficacy of iTBS and rTMS in promoting motor function recovery in individuals with cSCI. In addition, it seeks to identify the most effective stimulation site—motor cortex, SC, or a combined approach—for optimizing therapeutic outcomes. The study will further assess the impact of these TMS protocols along with customized rehabilitation programs on sensory and locomotor function, cortical excitability and neuroplasticity, SCI-related biomarkers, and self-reported outcomes, including pain, anxiety, depression, and overall quality of life.

## Methods

### Study Design

A double-blinded, prospective, randomized, placebo-controlled study will be conducted. The computer-generated sequence will be sealed in sequentially numbered envelopes, which will be opened after the patient is enrolled in the study. Both the patient and investigator will be blinded to the intervention. An experienced therapist will perform the intervention protocol. This protocol is based on the SPIRIT (Standard Protocol Items: Recommendations for Interventional Trials) guidelines (checklist provided in Multimedia Appendix 1).

### Duration of the Study

The recruitment, intervention, and follow-up phase will be 2 years, followed by 6 months of data analysis. Patient recruitment will start in January 2023 and the trial will be completed by July 2025.

### Inclusion and Exclusion Criteria

Adults aged 18 to 60 years with a thoracolumbar (T1-L5) SCI and complete motor loss below the lesion level (American Spinal Injury Association [ASIA] score A) will be screened and recruited within 1 month of injury.

Exclusion criteria include patients with osteoporotic fractures, a history of neurological or orthopedic diseases affecting the SC, head injuries, ferromagnetic metallic implants near the target stimulation area, pacemakers, cognitive impairment, pregnancy, a history of seizures, or acute eczema or bedsores.

### Confidentiality

The personal privacy of patients will be protected. The results of this study will not disclose any identifying and personal information of the patient without his or her permission.

### Sample Size

The sample size for this study is determined based on the methodology outlined by Roy et al [8], which assessed the reduction in motor evoked potential (MEP) amplitude following intervention. Using an α level of 0.05 and a power of 90%, these parameters are incorporated into the 2-tailed formula for sample size calculation.

For a 2-sample comparison of means, the null hypothesis (H0: m1=m2) will tested, where m1 and m2 represent the means of 2 distinct populations. The assumptions for the calculation are as follows:

α=.05 (2-sided), Power=0.90, m1=12.85, m2=13.53, SD1=0.3, SD2=0.3, n2/n1=1.00

Based on these assumptions, the estimated required sample size is calculated to be 6 subjects per group. To account for potential dropouts, a 20% adjustment is applied, resulting in a revised sample size of 8 participants per group. Consequently, the total minimum sample size required for the study is 40 participants.

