### Outcomes

#### Primary Outcome (Neurological)

The primary outcome will measure the severity of injury with the ASIA Scoring System. The ASIA impairment score (AIS) ranges from complete loss of sensation and movement (AIS=A) to normal neurological function (AIS=E). The ASIA motor score uses a test of the strength of 10 key muscles on each side of the body (eg, elbow flexors, wrist extensors, hip flexors, quadriceps, and dorsi flexors). The score ranges from 0 (no contraction) to 5 (normal resistance) through a full range of motion. A total possible score of 50 for the upper extremities and 50 for the lower extremities may be obtained [11]. The ASIA sensory score involves pinprick and light touch sensation at key points representing each dermatome of the body, scored on a 3-point scale (0, 1, and 2). Scores are summed to give a total possible score of 224, where a higher score indicates better sensation than a lower score.

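### The 90% power is calculated for a secondary MEP measure; for the primary ASIA outcome the protocol demonstrates no power

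*Protocol article*

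**What the plan says.** The Sample Size section of the protocol article contains the trial's only power calculation. It rests on a cited study "which assessed the reduction in motor evoked potential (MEP) amplitude following intervention" and tests two means with "α=.05 (2-sided), Power=0.90, m1=12.85, m2=13.53, SD1=0.3, SD2=0.3, n2/n1=1.00". The two means have no unit and no label saying which variable or condition each belongs to. The section concludes that "the estimated required sample size is calculated to be 6 subjects per group", raises this to 8 for 20% dropout, and multiplies by five groups to reach 40.

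The Outcomes section says: "The primary outcome will measure the severity of injury with the ASIA Scoring System". It then describes the ASIA impairment grade, the motor score and the sensory score. The TMS measures, including those built on MEPs, come under Secondary Outcomes, in Electrophysiological Parameter Outcomes.

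Statistical Analysis plans repeated-measures ANOVA, or nonparametric tests for skewed data, with Bonferroni or Tukey adjustment of pairwise comparisons. The primary analysis is intention-to-treat, with baseline values carried forward where data are missing. Limitations says in general terms that the small sample may reduce power.

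**The concern.** A power statement belongs to one endpoint, one effect size and one SD. Here all three come from an MEP study, while the trial is to be judged on the ASIA score. The protocol gives no ASIA difference, SD or conversion rate, and no argument that an MEP difference of 0.68 corresponds to any ASIA change. Yet the 90% is stated for the trial without restriction.

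The assumed effect is also very large. With "SD1=0.3, SD2=0.3" the two means lie more than two SDs apart, and only an effect of that order makes 6 per group sufficient. If a realistic ASIA effect is smaller in SD units, a non-significant primary result would be weak evidence, and a reader relying on the stated 90% could give it too much weight.

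**Working it through.** **Inputs (Sample Size section).** Two-sided alpha 0.05; power 0.90; means 12.85 and 13.53; SD 0.3 in both groups; 1:1 allocation; dropout 20%; five groups.

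**Step 1: reproduce the plan's figure.**

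- Difference: 13.53 − 12.85 = 0.68. Standardized effect: d = 0.68 / 0.3 = 2.27.
- Normal approximation: n = 2(1.96 + 1.2816)² / 2.267² = 4.09, rounded up to 5 per group.
- Two-sample t-test (noncentral t, df = 2n − 2, noncentrality d√(n/2)): power is 87.9% at n = 5 and 94.2% at n = 6. The smallest n reaching 90% is therefore 6, as stated.
- Dropout: 6 / (1 − 0.20) = 7.5, rounded up to 8. Total: 8 × 5 = 40.

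The stated 6, 8 and 40 are all reproduced, so there is no arithmetic error.

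**Step 2: look for the same inputs for the primary outcome.** None are given. The power for ASIA therefore cannot be computed from the document; only its dependence on an assumed effect can be shown.

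**Step 3: illustration.** Same t-test, one pairwise comparison, two-sided alpha 0.05 without correction. The effect sizes are assumptions and are not taken from the protocol.

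| Assumed difference (SD units) | Power, 8 per group | Power, 6 per group | n per group for 90% |
|---|---|---|---|
| 0.5 | 15% | 12% | 86 |
| 0.8 | 32% | 24% | 34 |
| 1.0 | 46% | 35% | 23 |
| 1.5 | 80% | 65% | 11 |
| 2.0 | 96% | 88% | 7 |

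Smallest difference detectable:

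| Analysed per group | 80% power | 90% power |
|---|---|---|
| 8 | 1.51 SD | 1.74 SD |
| 6 | 1.80 SD | 2.08 SD |

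**Step 4: effect of the planned multiplicity correction.** Five groups give 5 × 4 / 2 = 10 pairs, so full Bonferroni uses 0.05 / 10 = 0.005. Even at d = 2.27, the two-sample t-test then has about 86% power with 8 per group and 64% with 6. The stated 90% is thus a figure for a single two-group comparison at 0.05.

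**The case against.** The strongest reply is that the figures in Step 3 are not the power of the planned analysis. That is fair. The plan is repeated-measures ANOVA over five groups, not one t-test at one visit. Pooling the error over five groups of 8 (df = 40 − 5 = 35) lowers the detectable difference from 1.51 and 1.74 SD to about 1.44 and 1.67 SD, and baseline and repeated measurements could change it further. Pooling also softens Step 4: at d = 2.27 and alpha 0.005, 8 per group with df 35 gives about 93%. In addition, the primary analysis carries baseline forward, so all 8 per group are analysed and the rows for 6 describe a completer analysis. Against that, carrying baseline forward counts a patient without follow-up data as unchanged, which tends to dilute a true improvement. None of this supplies an ASIA effect or SD, so the mismatch stands.

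It can also be said that Limitations already concedes reduced power. It does so only in general terms, and the Sample Size section still gives 90% without confining it to MEP.

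Some stronger readings are tempting but not supported:

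- **That the trial is shown to be underpowered for ASIA.** The document gives no ASIA effect, and a true difference of about 1.74 SD or more would be detected with 90% power.
- **That a reduction is contradicted by m2 exceeding m1.** The protocol does not say which mean belongs to which condition, so m1 may be the reduced value.
- **That a before-after change was used as a between-group difference, or that 0.3 is really a standard error.** The protocol describes two distinct populations and labels 0.3 as an SD. Neither suspicion can be tested without the cited study.

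**Conclusion.** The point holds as a mismatch between the endpoint used for sizing and the primary endpoint. The 90% power applies to an MEP measure with an assumed effect of 2.27 SD and a single two-group comparison. For the ASIA score the protocol demonstrates no power.

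The size of the problem depends on the true ASIA effect, which the document does not give. Under the simple t-test illustration, 8 per group suits differences of about 1.5 to 1.7 SD or more and leaves power between 32% and 46% at 0.8 to 1.0 SD. Multiplicity correction lowers pairwise power further; pooled error and repeated measurements may recover part of it. That the means are MEP values is itself inferred from the sentence introducing the cited study, because the figures carry no label. The unrestricted power claim should be corrected before results are reported.

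**What to change.** Keep N = 40 and change the wording:

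1. In Sample Size, say that the 90% applies only to the MEP measure, giving its label and unit and which mean belongs to which condition, and only to one two-group comparison at 0.05. Alternatively, delete the claim.
2. In Primary Outcome, have the authors name which ASIA component and which time point is primary. The protocol describes several components and assessments after the intervention and at 1, 2 and 3 months without selecting one; the choice is theirs.
3. State the difference in that measure that 8 per group can detect, in SD units and in score points if an SD is available, under the planned analysis and multiplicity correction.
4. Unless that difference can be justified as plausible, describe the ASIA comparison as exploratory and present estimates with 95% CIs as the main result.

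The cost is text in the protocol and analysis plan and a less favourable stated power. No additional patients are needed.

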### Experimental Groups

A total of 40 patients will be randomized into 5 groups using computer-generated random numbers. Patients will be categorized into placebo, rTMS, and iTBS to evaluate the efficacy of iTBS versus traditional rTMS on the primary motor cortex (MC). To determine the optimal site for iTBS application, stimulation was given at either MC or SC or combined MC+SC.

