### Limitations

While this study offers valuable insights, several limitations must be acknowledged that may affect the interpretation and broader application of the findings. First, the sample size is relatively small, which could reduce the statistical power and may not fully represent the broader population of individuals with SCIs. Second, variability in the severity of SC injuries among participants may influence the outcomes, as responses to treatment could differ based on the level and completeness of the injury. Finally, the short duration of the follow-up period may not adequately capture the long-term effects of the interventions, suggesting the need for longer-term studies to assess the sustainability of the benefits observed.

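### No stated restriction on the random list secures 8 per group, and injury level, which the protocol says may affect response, enters neither the stated allocation nor the stated analysis

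*Protocol article*

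**What the plan says.** Allocation is described in two places in the protocol article. Experimental Groups: "A total of 40 patients will be randomized into 5 groups using computer-generated random numbers". Study Design: "The computer-generated sequence will be sealed in sequentially numbered envelopes, which will be opened after the patient is enrolled in the study". Neither names a block size, a stratum, a minimisation rule or a fixed number per arm. Neither calls the randomisation simple or unrestricted.

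The Sample Size section rests on equal arms. Its inputs are "α=.05 (2-sided), Power=0.90, m1=12.85, m2=13.53, SD1=0.3, SD2=0.3, n2/n1=1.00", it finds 6 per group, and it allows for dropout, "resulting in a revised sample size of 8 participants per group", which makes 40 over five groups.

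Inclusion and Exclusion Criteria admits thoracolumbar injuries from T1 to L5, all ASIA A. The Limitations section says that "responses to treatment could differ based on the level and completeness of the injury". Statistical Analysis plans a repeated measures ANOVA with post hoc pairwise comparisons, and a Friedman test for skewed data. It names no term for injury level.

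**The concern.** Two separate things are at issue.

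- **Arm size.** The sample size depends on 8 per arm. Random numbers give equal arms only if the list is restricted, and no restriction is stated.
- **Injury level.** The primary outcome is the ASIA motor and sensory score. The level of a complete injury determines how many key muscles and dermatomes are intact at baseline and how many remain to recover. In arms of about 8, a chance difference in level between two arms can look like an effect of stimulation mode or site. Comparing sites is a stated objective, and all pairs of arms are open to post hoc comparison, so the worst-balanced pair matters as well as a typical one.

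**Working it through.** **Inputs from the article.** N = 40, five arms, ratio 1:1, two-sided α 0.05, power 0.90, difference 13.53 − 12.85 = 0.68, SD 0.3, dropout 20%, levels T1 to L5. The article gives no split by level. A lumbar share of 20-40% (8, 12 or 16 of 40) is an assumption.

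**1. The plan's own figure.** The standardised difference is 0.68/0.3 = 2.267. Two-sample t power (noncentral t) is 0.879 at 5 per group and 0.942 at 6, so 6 is needed. Then 6/0.8 = 7.5, rounded up to 8, and 8 × 5 = 40. The stated figures reproduce.

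**2. Arm sizes, only if the list is unrestricted.** Sizes are then multinomial (40; 0.2 for each arm).
- P(8 in every arm) = 40!/(8!⁵ × 5⁴⁰) = 0.00084, or 0.08%.
- SD of one arm's size = √(40 × 0.2 × 0.8) = 2.53.
- By simulation, some arm has 5 or fewer in 67% of trials and 4 or fewer in 36%.

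**3. What that does to power, on the protocol's inputs.**

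| Arms | Power |
|---|---|
| 8 v 8 | 0.988 |
| 5 v 8 | 0.951 |
| 4 v 8 | 0.914 |
| Mean over a pair, unrestricted list, before loss | 0.963 |
| Mean over a pair, unrestricted list, after independent 20% loss | 0.90 |
| Mean over a pair, exactly 8 per arm, after independent 20% loss | 0.94 |

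Unequal arms alone therefore cost an average comparison a few points of power.

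**4. Injury level with exactly 8 per arm and no stratification.** For L lumbar patients among 40, the chance that two named arms hold a and b of them is C(8,a) × C(8,b) × C(24, L−a−b) / C(40, L). Summing over |a − b| ≥ 3 gives the named-pair column. The same counting over all five arms gives the other two.

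| Lumbar patients of 40 | Named pair differs by ≥ 3 | Some pair differs by ≥ 3 | Some pair differs by ≥ 4 |
|---|---|---|---|
| 8 | 12% | 57% | 16% |
| 12 | 18% | 70% | 30% |
| 16 | 21% | 70% | 39% |

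These figures hold even if the list delivers 8 per arm perfectly.

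**5. What blocking would give.** Blocks of 5: 40/5 = 8 complete blocks, hence exactly 8 per arm. Blocks of 5 within two level strata: if one stratum holds 5k + r patients (r from 1 to 4), the other holds 5(7 − k) + (5 − r). Each arm gets k + (7 − k) = 7 from complete blocks, plus at most one from each unfinished block, so 7 to 9. If r = 0, every arm has 8.

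**The case against.** The article never says the list was simple. A computer-generated sequence prepared in advance and sealed in numbered envelopes fits a blocked list, or a random permutation of 40 slots with 8 per arm, just as well, and the planned ratio of 1.00 points to equal arms. A condensed article may leave block details to the full protocol. This objection stands. A reader might infer that simple randomisation was used and that 8 per group is not delivered, but the documents do not show that.

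The power loss is also modest, even if the list was unrestricted. The primary analysis is by intention to treat with baseline values carried forward, so patients who drop out stay in the arm counts. The after-loss figures above model shrinking arms, which is not the stated primary analysis. This stands too.

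On level, it can be said that chance imbalance is not bias, that the article already lists variability by level as a limitation, and that stratifying 40 patients over five arms is a matter of preference. The first two are true, and the large percentages refer to the worst of ten pairs, not to a typical one. But acknowledging a limitation does not control it, and adjustment needs no stratified allocation.

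Finally, the Results section reports a start in January 2023 and analysis from January 2025, so few envelopes may remain. That weakens any remedy through allocation but not one through analysis.

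**Conclusion.** The point holds in two parts of unequal strength.

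- **Arm size: conditional.** No stated restriction secures 8 per group. The 0.08% and 67% figures apply only if the list was unrestricted. In that case mean power for a pair still stays at about 90% or above on the protocol's own inputs. This supports a request to report the method, not a claim that the arms are unequal.
- **Injury level: holds however the list was drawn.** The article admits T1 to L5 and says response could differ by level, but level appears in neither the allocation nor the analysis as described. With 8 per arm, some pair differs by 3 or more lumbar patients in 57-70% of trials, and a given pair in 12-21%. This rests on the assumed 20-40% lumbar share and a simple thoracic/lumbar split. How far such an imbalance would shift the ASIA scores cannot be computed from the article.

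**What to change.** 1. Include injury level (thoracic v lumbar, or neurological level) as a prespecified baseline covariate in the primary between-group analysis. Level is already known for every patient, so this works even if enrolment is over. The cost is about one degree of freedom: with 40 patients in five arms, 35 between-patient residual degrees of freedom become 34. The Friedman test has no place for a covariate, so the plan should also say how level is handled if the data are skewed.
2. Report the allocation method actually used, including any blocking or stratification.
3. For any patients not yet allocated, use permuted blocks of 5. Over all 40 patients this gives equal arms, or 7 to 9 per arm if stratified by level. Avoid mixing blocks of 5 and 10 within strata, because unfinished blocks can then leave arms of 5 to 11.

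The downside of a fixed block of 5 is that the therapist, who knows the treatment given, can partly predict the next allocation. The list should therefore be held by someone not involved in enrolment or assessment. No extra patients or procedures are needed.
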